# Partnering with general practitioners to optimize survivorship for patients with lymphoma: a phase II randomized controlled trial (the GOSPEL I trial)

**DOI:** 10.1186/s13063-020-04945-4

**Published:** 2021-01-06

**Keywords:** Lymphoma, Hematology, Shared care, Quality of life, Protocol, Randomized controlled trial

## Abstract

**Background:**

Survival rates for lymphoma are highest amongst hematological malignancies. In 2019, it was estimated that over 6400 Australians were diagnosed with lymphoma, a group of hematological malignancies with a high 5-year survival rate of ~ 76%. There is an increased focus on the promotion of wellness in survivorship and active approaches to reducing morbidity related to treatment; however, current models of follow-up care heavily rely on hospital-based specialist-led care.

Maximizing the potential of general practitioners (GPs) in the ongoing management of cancer is consistent with the national health reform principles and the Cancer Council Australia’s Optimal Care Pathways. GPs are well positioned to provide guideline-based follow-up care and are more likely to address comorbidities and psychosocial issues and promote healthy lifestyle behaviors. This study aims to test the feasibility of the GOSPEL I intervention for implementing an integrated, shared care model in which cancer center specialists and community-based GPs collaborate to provide survivorship care for patients with lymphoma.

**Methods:**

We describe a protocol for a phase II, randomized controlled trial with two parallel arms and a 1:1 allocation. Sixty patients with Hodgkin’s and non-Hodgkin’s lymphoma will be randomized to usual specialist-led follow-up care (as determined by the treating hematologists) or a shared follow-up care intervention (i.e., GOSPEL I). GOSPEL I is a nurse-enabled, pre-specified shared care pathway with follow-up responsibilities shared between cancer center specialists (i.e., hematologists and specialist cancer nurses) and GPs. Outcome measures assess feasibility as well as a range of patient-reported outcomes including health-related quality of life as measured by the Functional Assessment of Cancer Therapy—Lymphoma, patient experience of care, symptom distress, comorbidity burden, dietary intake, physical activity behaviors, financial distress/interference, and satisfaction of care. Safety indicators including hospital admission and unscheduled lymphoma clinic visits as well as process outcomes such as intervention fidelity and economic indicators will be analyzed.

**Discussion:**

This trial is designed to explore the feasibility and acceptability of a new model of shared care for lymphoma survivors. Patient-reported outcomes as well as potential barriers to implementation will be analyzed to inform a larger definitive clinical trial testing the effects and implementation of a shared care model on health-related quality of life of lymphoma survivors.

**Trial registration:**

Australia and New Zealand Clinical Trials Registry ACTRN12620000594921. Registered on 22 May 2020.

## Administrative information

The order of the items has been modified to group similar items (see http://www.equator-network.org/reporting-guidelines/spirit-2013-statement-defining-standard-protocol-items-for-clinical-trials/).

**Table Taba:** 

Title {1}	Partnering with General practitioners to optimize Survivorship for patients with Lymphoma: A phase II randomized controlled trial (The GOSPEL I Trial)
Trial registration {2a and 2b}.	Registry Name: Australia and New Zealand Clinical Trials Registry. Trial Identifier: ACTRN12620000594921. All SPIRIT items can be found within the body of the protocol.
Protocol version {3}	03/08/2020, Version 1.5
Funding {4}	This study is funded by a Health Innovation, Investment and Research Office (HIIRO). Queensland Advancing Clinical Research Fellowship

## Introduction

### Background and rationale {6a}

In 2019, it was estimated that over 6400 Australians were diagnosed with Hodgkin’s lymphoma (HL) and non-Hodgkin’s lymphoma (NHL) [1]. Lymphomas are hematological malignancies with high overall 5-year survival rates (~ 76%) resulting in a large cohort of people post therapy or undergoing regular surveillance for incurable but indolent disease not yet warranting treatment. Lymphoma survivors require ongoing survivorship care including monitoring for cancer progression or recurrence, surveillance for secondary/new primary cancer, and management of a range of long-term bio-psycho-social effects from their cancer diagnosis and treatment. Moreover, many cancer survivors are also in need for management of comorbidities [2]. Compared to people without cancer, people with cancer are more likely to develop mental and behavioral problems (2.5 times), circulatory conditions (1.3 times), musculoskeletal conditions (1.4 times), and endocrine system disorders (1.2 times) [2]. These health concerns highlight the importance of a well-integrated, patient-centered model of care that addresses cancer-related survivorship needs as well as comorbidities for people who have been diagnosed with lymphoma.

The current models of cancer care in Australia are mostly specialist-led and focus on surveillance for disease recurrence, rather than holistic care needs. These models of care limit integration between specialist institutions and the patient’s community-based general practitioner (GP), also called family physician or primary care physician in some countries. With the ever-growing and aging population of cancer survivors, specialist-led follow-up is not optimal as it does not encourage an integrated, patient-centered approach in which comorbidities and long-term effects experienced by cancer survivors can be effectively managed. Specialist-led follow-up does not capitalize on the expertise of GPs, and it requires patients living in the rural/regional areas to travel long distances to the cancer centers.

Ongoing care of patients with chronic illnesses such as cancer is core business for general practice. Maximizing the potential of GPs in the ongoing management of cancer is consistent with the national health reform principles [3–5] and the Optimal Care Pathways [6, 7]. In the breast cancer setting, it is clear that GPs can provide guideline-based follow-up care and are more likely to address comorbidities and psychosocial issues and promote healthy lifestyle behaviors compared to cancer specialists [8]. Shared care arrangements might also facilitate a smoother transition to “mainstream” clinical care for patients who have successfully undergone treatment and had several years of follow-up without recurrence. A shared care approach is likely to be more cost-effective than a specialist-led model due to the added benefits from harnessing the expertise of both the cancer specialist as well as the GP. Such an approach, if effective, may further relieve pressures in health services to meet the ever-increasing demand. The recent COVID-19 pandemic has further highlighted the need to explore, implement, and evaluate alternative models of care, enabling a reduction in acute hospital setting presentations and enhanced community GP involvement [9].

Although implementing an integrated, shared care follow-up model is the next logical step for cancer patients with high survival rates, the evidence base supporting this model is less established for lymphoma compared to breast cancer. There are two key reasons that a shared follow-up care model between specialists and GPs is not routinely implemented for lymphoma survivors across Australia. Firstly, randomized controlled trials (RCT) evidence for the effectiveness and cost-effectiveness of a shared care model between specialists and GPs for lymphoma are *not* yet established [10]. Secondly, a number of barriers to shared care between the acute cancer care setting and GPs have been reported [11, 12]. These include, but are not limited to, the lack of a coordinator who drives a shared model involving multiple providers, lack of patient and provider knowledge about the benefits of shared care and how to implement it, insufficient or delayed communication between cancer specialists and GPs, and lack of awareness of available support such as funding models, tools and resources [11–13]. These barriers might be overcome if a specialist cancer nurse (SCN) advises stakeholders of the benefits of shared care (patient and GPs) and facilitates effective and timely care coordination and communication by acting as the conduit between the specialist cancer multidisciplinary team and the GPs at key transition time points (such as completion of treatment) [14].

### Objectives {7}

The objective of the study is to test the feasibility of a prospective, pragmatic, randomized controlled trial (RCT) of the *GOSPEL I* intervention—an integrated, shared care model involving hematologists and GPs for lymphoma follow-up.

### Trial design {8}

This single-center, phase II pilot RCT aims to assess the feasibility of a larger definitive clinical trial. Outcome data will be collected at three points: (*t*_*1*_) baseline (at enrolment), (*t*_*2*_) 6 months, and (*t*_*3*_) 12 months.

## Methods: participants, interventions, and outcomes

### Study setting {9}

This study is to be conducted in Princess Alexandra Hospital—a large, Australian metropolitan tertiary teaching hospital and involves general practices of the surrounding areas.

### Eligibility criteria {10}

Due to the varying follow-up requirements for patients with lymphoma, the study population consists of two groups of patients who require two distinct follow-up pathways. Group one (post-treatment follow-up) consists of patients with a histopathologically confirmed diagnosis of aggressive or indolent lymphoma in the acute post-treatment phase (i.e., within 3 months of completion of chemotherapy). Group two (observation follow-up) consists of patients with a histopathologically confirmed diagnosis of indolent lymphoma followed up in the surveillance clinic who are at least 2 years post-treatment or treatment naïve. In addition to meeting one of the group descriptions above, participants must also meet all of the following criteria to be eligible for inclusion: ≥ 18 years of age, have an Easter Cooperative Oncology Group (ECOG) performance status < 2, be an ambulatory outpatient at the time of recruitment, be able to nominate a GP or GP clinic to be involved in their follow-up, have access to a telephone, and be able to speak and read English. Patients meeting any of the following criteria are excluded: the presence of severe mental, cognitive or physical conditions that would limit the patient’s ability to participate as per treating clinician, lymphoma not in remission (applicable for group 1 only), and patients receiving maintenance treatment.

### Who will take informed consent? {26a}

Treating clinicians will identify potentially eligible patients, obtain their consent to be contacted by the research team, and refer them to the research nurse; the research nurse will contact the patient and provide the patient with full information of the study including its purpose, procedures, expected duration, and the potential benefits, risks, and inconveniences in participation both verbally and in the form of the “Participant Information and Consent Form” (PICF). Prior to being asked to sign the consent form, patients will be given ample opportunity to ask questions and decide whether to participate in the study. All questions about the study will be answered to the satisfaction of the patient. Prior to participation, the written PICF will be signed and personally dated by the patient and the research nurse who conducted the informed consent discussion. The patient will receive a copy of the signed and dated PICF.

### Additional consent provisions for collection and use of participant data and biological specimens {26b}

Not applicable. This trial does not involve collecting additional participant data or biological samples for storage. There are no plans for ancillary studies using data collected in this trial.

## Interventions

### Explanation for the choice of comparators {6b}

With the ever-growing population of cancer survivors, the specialist model of follow-up is insufficient and unsustainable. The shared care model between specialists and GPs focuses on the complex care needs of lymphoma survivors, encompassing the strengths and expertise of multiple providers [10]. It has the potential to contribute to better patient health outcomes as well as reducing the strain on overcrowded hospital-based outpatient services. Effective shared care in the hematology setting relies on establishing and maintaining ongoing communications channels [10]. It is also proposed that transition to primary care occurs via a specialist nurse to ensure key components of survivorship care are addressed and communicated to health care providers [15]. These key considerations have been incorporated in the intervention described below.

### Intervention description {11a}

#### Arm 1

Participants who are randomized to the usual care arm will receive standard follow-up care plus a survivorship booklet on “Living Well After Treatment—A guide for patients and families” published by Leukaemia Foundation [16]. This booklet was designed by our research team in collaboration with expert clinicians and consumers via the Leukaemia Foundation. The current follow-up arrangement is a specialist-led model as determined by the treating hematologist.

#### Arm 2

Gospel I. Participants who are randomized to the GOSPEL I arm will receive a multi-faceted intervention that includes a pre-specified shared care pathway for follow-up. The design of the GOSPEL I is informed by a number of clinical guidelines [i.e., National Comprehensive Cancer Network [17] and European Society of Medical Oncology [18–20]], the Optimal Care Pathway for HL and Diffuse Large B-Cell Lymphoma (DLBCL) [21], the self-efficacy model [22, 23], and the Capabilities for Supporting Prevention and Chronic Condition Self-Management framework [24]. Table 1 outlines the active ingredients of the intervention.

**Table 1 Tab1:** Active ingredients of GOSPEL I model of care intervention for patients allocated to receive the GOSPEL 1 intervention

Active ingredient	Personnel involved	Activities
**Pharmacy review** Duration: Up to 20 min Mode: Teleconference	Pharmacist and the patient	• Obtain and record medication history including cancer and non-cancer therapy ***Note****: The pharmacy review will be offered to all patients in the intervention arm and will be provided via teleconference or phone call based on the patient’s preference. Medication history completion (Y/N) will be recorded by the RN as a process measure and will therefore not be considered a protocol violation should patients decline this service.*
**SCN-led clinic** Duration: 60 min Mode: Teleconference or face to face	Specialist cancer nurse and the patient	• Treatment summary including follow-up appointment schedule • Co-developing the SCP (including planning for health goals) • Post-treatment education ***Note****: The completed draft SCP will be sent to the GP prior to the case-conference. The research team or SCN will organize the case conference with the GP.*
**GP case conference and optional “booster” case conference** Duration: Maximum 40 min Mode: Teleconference	SCN, GP (± one more healthcare professional).	• The SCN will present the Treatment Summary, and the draft Survivorship Care Plan. • The SCN will negotiate follow-up responsibilities with the GP and will • Answer any questions the GP may have. • Additional education and support to the GP ± practice nurse if applicable regarding physical examination and blood analysis. ***Note****: A copy of the completed and agreed Survivorship Care Plan provided to the GP and the patient and scanned for IeMR. Where a full case conferencing is not possible, all efforts will be made to facilitate a teleconference of a shorter duration (~ 5 min) to deliver all key information on the Survivorship Care Plan. An additional “booster” case conference will be offered to GPs based on their preference should they require further support prior to participating in lymphoma surveillance activities.*
**Standardized shared follow-up care** Mode: Face to face	GP, SCN, patient, hematologist	• The cancer specialist will review the patient history (i.e., fevers, sweats, loss of weight, infections), conduct a physical examination (i.e., lymphadenopathy, hepatosplenomegaly), and order/review blood tests (i.e., FBC, U+Es, LFTs LDH). • GPs who agree to participate in all aspects of follow-up care will review the patient history (i.e., fevers, sweats, loss of weight, infections), conduct a physical examination (i.e., lymphadenopathy, hepatosplenomegaly), and order/review blood tests (i.e., FBC, U+Es, LFTs LDH). • As a safety measure the SCN/RN will ensure that surveillance activity is conducted as per clinical guidelines. Where the GP is unable to complete this activity, the SCN will ensure surveillance activity is transferred to the acute cancer center/specialist. This will be documented as a process measure or future studies in this area. • The GP will also carry out care activities outlined in the SCP. • The GP will follow an escalation pathway which utilizes the SCN as the rapid access point for rapid re-entry to the acute setting and point of contact for the GP for support and resources. ***Note****: The GP will be given the direct telephone number of the SCN responsible for the patient. At any time if the GP becomes concerned about the patient, he/she can ring the SCN for advice or request escalation to acute care for review.*

*Abbreviations*: *SCN* specialist cancer nurse, *SCP* Survivorship Care Plan, *GP* general practitioner, *IeMR* integrated electronic medical records, *FBC* full blood count, *U&E* urea and electrolytes, *LFT* liver function tests, *LDH* lactate dehydrogenase

After enrolment, participants in the intervention arm will receive a consultation with a specialist cancer nurse to provide a treatment summary, the shared follow-up care appointment schedule, and survivorship patient education (including the survivorship booklet on “Living well After Treatment” published by the Leukaemia Foundation) [16] and co-develop a draft Survivorship Care Plan (SCP) with the patient. The SCP will include up to three SMART (Specific, Measurable, Achievable, Realistic and Timely) goals using motivational interviewing and self-efficacy techniques. The treatment summary and draft SCP will be provided to the GP.

Within 4 weeks of the specialist cancer nurse consultation, a case-conference at a mutually agreed time (maximum of 40 min) between the specialist cancer nurse and the patient’s nominated GP will be completed to communicate the treatment summary, negotiate responsibilities of the shared-follow-up care schedule, and negotiate the GP’s role in facilitating the SCP goals. The GP may propose changes or express if they are unable to take part in specific care activities outlined in the SCP. The finalized SCP will be filed in the patient’s medical records and provided to the patient and the GP. As a safety measure, the SCN will ensure that surveillance activities are conducted as per clinical guidelines. Where the GP is unable to complete any of these activities, the SCN will ensure these surveillance activities are transferred to the acute cancer center/specialist. This will be documented as a process measure for future studies in this area.

The GP will also be provided with an escalation pathway which utilizes the SCN as the immediate access point for rapid re-entry to the acute setting and point of contact for the GP for support and resources. The SCN thus plays a key role in providing resources to support the GP ± practice nurse in carrying out all activities outlined in the SCP.

### Criteria for discontinuing or modifying allocated interventions {11b}

The presence of any of the following criteria constitutes cause for the withdrawal of the participant: altered mental capacity resulting in inability to provide continuing informed consent, notification from treating oncologist and or GP that participant is not deemed to have capacity to consent, and recurrence or progressive disease or death.

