#### Plans to promote participant retention and complete follow-up {18b}

Participants who deviate from the protocol will not be withdrawn from the trial. Participants who withdraw from the trial nominate the degree to which they withdraw (i.e., whether they withdraw from active data collection ± passive data collection such as hospital records). To avoid losing participants to follow-up, contact information of a friend or family member will be requested as a back-up contact in case of difficulty in contacting the participant. Provision of a contact is not mandatory and will not result in exclusion from the trial.

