## Statistical methods

### Statistical methods for primary and secondary outcomes {20a}

Descriptive statistics will be used to report on feasibility and process-related elements (e.g., recruitment, intervention, retention rates) as well as clinical and resource outcomes. Preliminary effect size estimates for patient and resource use outcomes will be calculated following intention-to-treat principles using linear mixed models. Models will include group, time, and their interaction and be adjusted by diagnosis and age. Balance of demographic variables between usual care and intervention group will be investigated using chi-square and *t* test and will be included in the model if found to be both significantly associated with the outcome and confounding the intervention. Assumptions of all models (normality, linearity, homoscedasticity) will be examined using the residuals of the model and will be described using mean, median, skewness, kurtosis, and plots such as histograms and QQ-plots. If assumptions are violated, models will be either bootstrapped or log transformation as appropriate.

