### Methods in analysis to handle protocol non-adherence and any statistical methods to handle missing data {20c}

Any discrepancies and missing data will be alerted and resolved with the relevant research team member(s) as soon as practical. All electronic CRFs will be maintained on the system with details of any changes logged accordingly. Preliminary effect size estimates for patient and resource use outcomes will be calculated following intention-to-treat principles using linear mixed models. Patterns of missing data will be examined using chi-square and *t* tests. Missing data for the outcomes will be accounted for by using mixed models allowing the use each available case by computing maximum likelihood estimates.

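### Recurrence or progression withdraws the participant rather than only the intervention, and the protocol does not say that outcome collection continues

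*Protocol article*

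**What the plan says.** All references are to the Protocol article.

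- **Item 11b** (criteria for discontinuing or modifying the allocated intervention) states: "The presence of any of the following criteria constitutes cause for the withdrawal of the participant". The list covers loss of capacity to consent, notification of such loss by a clinician, "and recurrence or progressive disease or death". The rule is not limited to one arm.
- **Item 18b** (retention) states: "Participants who deviate from the protocol will not be withdrawn from the trial". It then lets those who withdraw choose how far they do so, separating active collection from passive collection through hospital records.
- **Items 20a and 20c** promise effect estimates for patient and resource-use outcomes "following intention-to-treat principles using linear mixed models". The model has group, time and their interaction, adjusted for diagnosis and age. Item 20c adds: "Missing data for the outcomes will be accounted for by using mixed models", using maximum likelihood on the available cases.
- **Items 12 and 18a** (Tables 3 and 4) schedule the FACT-Lym and most other patient-reported outcomes at baseline, 6 and 12 months. Safety indicators are counts from hospital records, placed at the 18-month close-out. Neither table lists recurrence or progression as an outcome.
- **Item 22** states that adverse events will not be reported.

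**The concern.** The heading of item 11b concerns the intervention, but its sentence removes the person. If the sentence is followed, later questionnaires are lost because of a health event after randomization. Patients who progress probably report worse quality of life than their earlier scores predict, and progression is not a term in the stated model, so missing at random is a doubtful assumption for these losses.

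The loss may also differ by arm. In shared care, GPs who agree take on history, examination and blood tests (Table 1), so who carries out surveillance is part of what is randomized. The time at which recurrence is found, and therefore the time of withdrawal, could differ too.

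With no adverse event reporting, the hospital-record counts are the main safety information. If record extraction stopped at recurrence, later encounters would be missing from the safety and resource counts. Retention, one of the feasibility figures in item 20a, would also mix disease events with ordinary drop-out.

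**Working it through.** **Step 1: does item 11b end follow-up or only the intervention?** The heading supports the second reading and the sentence supports the first. Two features favour the sentence:
- The same list contains loss of capacity and death, which end participation altogether.
- The rule also applies to usual care, where the study adds only a booklet, so withdrawal there can hardly mean anything but leaving follow-up.

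Nothing in the article says that questionnaires continue after recurrence.

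**Step 2: does item 18b resolve it?** Only in part. Deviators stay in, and a participant who withdraws may allow record collection to continue. Item 18b does not say whether that choice extends to a withdrawal triggered by item 11b.

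**Step 3: size.** The plan gives no figure to reproduce: no event rate, SD, effect size or power. The only input from the document is 30 per arm, 60 in total. Everything else here is an assumption.

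*Participants affected.* Assume 5% to 20% recur or progress within 12 months:
- 60 × 0.05 = 3
- 60 × 0.20 = 12

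If these count as withdrawals, retention falls by 5 to 20 points without anyone choosing to leave.

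*Precision.* The 95% half-width for a 12-month difference, in SD units and ignoring any gain from repeated measures, is 1.96 × √(2/n):

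| Assumed loss | n per arm | Half-width (SD) |
|---|---|---|
| 0% | 30 | 0.51 |
| 5% | 28.5 | 0.52 |
| 10% | 27 | 0.53 |
| 20% | 24 | 0.57 |

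*Shift in the arm difference.* Let D be the amount by which progressors' true scores fall below the model's prediction, the same in both arms. The shift is D × (p_shared − p_usual). Assume D = 0.5 to 1.0 SD:

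| p_usual | p_shared | Shift, D = 0.5 | Shift, D = 1.0 |
|---|---|---|---|
| 10% | 10% | 0 | 0 |
| 10% | 15% | 0.025 | 0.05 |
| 10% | 20% | 0.05 | 0.10 |
| 5% | 20% | 0.075 | 0.15 |

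A 10-point difference between arms is 3 patients of 30. The mixed model removes the shift only to the extent that scores observed before withdrawal predict the later decline.

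**The case against.** The strongest reply is that this is a feasibility pilot without hypothesis testing. Its feasibility outcomes are recruitment and acceptability, and even the assumed shifts are small beside a half-width of about 0.5 SD. That stands, and it limits the weight of the point.

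A reader might infer more than the documents support:

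- **That outcomes are deleted.** Nothing discards collected data. Baseline scores and any earlier 6-month scores remain in the model, and the unscheduled visit or rapid referral that leads to the diagnosis would usually come before withdrawal.
- **That safety events are certainly lost.** Item 18b permits continued record collection. The gap is that its scope is unstated, so loss is possible but not established.
- **That intention-to-treat is flatly contradicted.** Participants can still be analysed as randomized. The tension lies in follow-up, not in the analysis set.
- **That the arm contrast is known to be biased.** No document figure shows that progression differs by arm.
- **That group two is the more exposed.** No rates are given for either group, and group one includes aggressive lymphoma soon after chemotherapy.
- **That listing death is a fault.** Death necessarily ends questionnaires.

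It may also be said that the heading makes the rule one about the intervention only. That reading is possible but fits the list and the usual-care arm poorly. If it is what was meant, the sentence still needs changing.

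**Conclusion.** The point holds as a moderate fault in a stated conduct rule. Items 11b, 18b and 20c do not fit together on whether data collection continues after recurrence or progression, and the literal text of item 11b ends it for the questionnaires. Whether hospital-record extraction continues is undefined.

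The bias cannot be quantified from the documents. It is about 0.05 to 0.10 SD if progression differs by 10 points between arms and D is 0.5 to 1.0 SD, and zero if rates and deficits are equal. The case for acting does not rest on that size. No analysis plan can recover questionnaires that were never collected, the record counts carry the safety information, and the definitive trial that this pilot is meant to inform could inherit the rule.

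**What to change.** Reconcile items 11b, 18b and 20c so that stopping the intervention and stopping data collection are separate decisions:

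- State that recurrence or progression is not in itself a reason to stop data collection. The 6- and 12-month questionnaires and hospital-record extraction continue unless the participant withdraws consent for either.
- State that the choice of degree of withdrawal in item 18b covers participants who meet an item 11b criterion.
- Report recurrence, progression and death by arm, separately from drop-out in the retention figure.

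This needs a short protocol amendment with ethics committee approval, and a case report form field for the disease event if none exists. The downside is that some patients will decline questionnaires after recurrence, so some missing data will remain. Nothing is proposed about care after recurrence or about when the shared care pathway should stop.
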